### Outcome measures

The primary outcome of this trial is the accuracy of LMP-recall dates. Accuracy of LMP-recall is defined as participants who will able to recall their start date of LMP within ±1 day of actual start date for their last menstrual cycle.

The secondary outcome of the trial is the certainty of LMP-recall dates. Participants will be asked to mention their level of certainty regarding their LMP-recall dates using the Likert scale ranging from 1 to 4 (highly certain, almost certain, somewhat certain, uncertain). Certainty will be defined if the participant are ‘highly certain’ regarding their recall for the last menstrual cycle.

Additionally we will also validate the LMP-dates recorded through the intervention tools with dates obtained from surveillance.

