### Sample size

Sample size has been calculated to observe a minimum of 30% relative change in the primary outcome measure. We used STATA (comparison of two proportions in the presence of clustering effect) for sample size calculation. Assuming that in the rural context of Bangladesh approximately 55% of women can accurately recall LMP (at baseline without any intervention) [13], to measure a 30% relative change in recall as an effect of the intervention, we will require 252 participants from 28 clusters per arm (5% level of significance and 90% power). Accounting for 15% refusal and 20% loss to follow-up, the adjusted sample size was 420 adolescents and 420 recently married women per arm (Table 2).

**Table 2 Tab2:** Sample distribution

Number of samples					
	Arm1: Control arm	Arm2: Counselling & calendar (C + C)	Arm3: Counselling & SMS (C + S)	Arm4: Counselling & smart phone application	Total
Recently married women	420	420	420	420	1680
Adolescent girls	420	420	420	420	1680

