### Methods of data collection, management and analysis

Data for this study is being collected in the following ways:(i)
*LMP surveillance*

Actual LMP-dates of the enrolled study participants are being collected at two time points through 3-month long surveillances.. The baseline LMP surveillance was done before the start of implementation of interventions whilst the endline will be done before the end of implementation. A tab-based LMP surveillance tool (specially designed for this study), is used by field surveillance workers to collect this information through fortnightly rounds. No other information will be elicited from the participants during LMP-surveillance.(ii)
*LMP surveys*

A baseline survey was conducted among enrolled adolescents and recently married women in all arms before the start of the implementation of interventions. Face-to face interviews were done by trained data collectors using a structured questionnaire to elicit the required information. Participants were asked to recall their past 3 months LMP dates and their level of certainty regarding the LMP-recall dates. Information regarding demographic characteristics (age, sex, education, occupation), household’s socioeconomic profiles (housing status, assets, monthly income, ownership of mobile phone & accessibility to mobile phone), menstrual history were also collected. Recently married women were additionally asked regarding the use of contraceptive, pregnancy and birth outcomes. A similar survey will be conducted at endline.(iii)
*Data*

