#### Data analysis

A participant flow diagram will be prepared following CONSORT 2010 guideline. Primary data analysis will be done on intention to treat basis. Analyses will be conducted at the individual level, and will be adjusted for cluster randomization.

For the primary outcome analysis, we will first examine the proportion of women accurately reporting LMP-dates at baseline and at endline. Differences in differences method will be used to ascertain the change. The analysis will be adjusted for confounders such as education, socio-economic status, and length of recall by bivariate analysis. Additionally, we will explore the change in mean and standard deviation of the difference between LMP-recall dates collected through LMP surveys and LMP-dates collected through LMP surveillance.

We will also validate the tools by comparing the distribution of LMP-dates recorded through the intervention tools with actual LMP-dates collected through LMP surveillance. Skewness and kurtosis tests of distribution of two LMP dates (recorded LMP and actual LMP) will be compared.

Stata® software version 10.1 (2008; Stata Corporation, College Station, TX, USA) will be used for all analyses.

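### Comparing the skewness and kurtosis of tool and surveillance dates does not measure whether a woman's recorded date matches her own actual date

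*Protocol article*

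**What the plan says.** The Outcome measures section of the protocol article names a primary outcome (accuracy of recall) and a secondary outcome (certainty of recall), and then adds: "Additionally we will also validate the LMP-dates recorded through the intervention tools with dates obtained from surveillance". The Data analysis section gives the method: "We will also validate the tools by comparing the distribution of LMP-dates recorded through the intervention tools with actual LMP-dates collected through LMP surveillance". The next sentence names the statistics: "Skewness and kurtosis tests of distribution of two LMP dates (recorded LMP and actual LMP) will be compared".

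A paired difference does appear in the same section, but for another comparison: "we will explore the change in mean and standard deviation of the difference between LMP-recall dates collected through LMP surveys and LMP-dates collected through LMP". That sets dates recalled in the surveys against the surveillance dates, and does not involve dates entered in the tools. The article states no within-woman measure for the tools.

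The trial has its own standard of accuracy, set for recall: "recall their start date of LMP within ±1 day of actual start date for their last menstrual cycle". It also has a reference date for each participant: "Actual LMP-dates of the enrolled study participants are being collected at two time points through 3-month long surveillances".

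**The concern.** Validating a recording tool means asking whether the date a woman entered is the date her period began. That is a question about pairs of dates. The planned statistics drop the pairing and compare the shapes of two pooled sets of dates. Two sets can have the same shape while hardly any woman's two dates agree.

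At stake is the meaning of a statement that a tool was validated. Similar skewness and kurtosis could be reported as support for a tool whose dates are a week out, against the trial's own ±1 day standard. Conversely, a difference in shape would not tell a reader how far out the dates are, or for how many women. Because the article names the statistics itself, this is more than a detail left to an analysis plan that is not shown.

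**Working it through.** The plan gives no figure to reproduce. The check is algebra followed by simulation.

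**1. Invariance (no assumption about the dates).** Skewness is E[(X − μ)³]/σ³ and kurtosis is E[(X − μ)⁴]/σ⁴.
- If every tool date is X + c, the mean becomes μ + c, each deviation X − μ is unchanged, and so are both statistics.
- If the dates are re-paired between women, the set of values is the same, so both statistics are the same.

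**2. Simulation.**
- n = 252, the per-arm number before inflation: "we will require 252 participants from 28 clusters per arm (5% level of significance and 90% power".
- True start dates uniform over 30 days. This is an assumption; the article fixes no window.
- 2,000 replicates; entries are means of tool minus actual.

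| Tool dates | Change in skewness | Change in kurtosis | Within ±1 day | Mean difference (days) | SD of difference (days) |
|---|---|---|---|---|---|
| Accurate (error at most 1 day) | 0.000 | +0.020 | 100% | 0.0 | 0.8 |
| Shuffled between women | 0.000 | 0.000 | 10% | 0.0 | 12.2 |
| Unrelated random dates | −0.001 (SD 0.13) | −0.003 (SD 0.11) | 10% | 0.0 | 12.2 |
| All 7 days late | 0.000 | 0.000 | 0% | 7.0 | 0.0 |
| All 14 days late | 0.000 | 0.000 | 0% | 14.0 | 0.0 |
| Random error, SD 7 days | +0.001 | +0.745 | 17% | 0.0 | 7.0 |
| Rounded to nearest ten | −0.040 | +0.240 | 30% | −0.2 | 2.9 |
| 40% enter one fixed date | +0.680 | +0.196 | 63% | −5.8 | 8.9 |

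The 10% for shuffled dates agrees with a direct count for two unrelated days out of 30: (30 + 2 × 29)/900 = 0.098.

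On shape alone, the shuffled and late tools match the actual dates at least as closely as the accurate tool does. The three columns on the right, which use the pairs, separate them at once.

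**3. The tests themselves.** In one simulated set of 252, the skewness test gave p = 0.32 and the kurtosis test p of about 2 × 10⁻⁴⁹. These p-values were the same for the true dates, the shuffled dates and the dates 7 days late. Agreement within ±1 day was 100%, 8% and 0%.

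**4. Random error depends on the window.** For dates uniform over W days, the variance is V = W²/12 and the excess kurtosis is −1.2. Adding independent normal error with SD s gives −1.2 × (V/(V + s²))². With s = 5:
- W = 90: V = 675; −1.2 × (675/700)² = −1.116; change 0.08.
- W = 30: V = 75; −1.2 × (75/100)² = −0.675; change 0.53.

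In both cases the share of whole-day dates within ±1 day is the same: P(|Z| < 1.5/5) = 0.24. The same error therefore gives a kurtosis change more than six times as large under one window as under the other. As a cross-check, s = 7 and W = 30 give −1.2 × (75/124)² = −0.439, a change of 0.76, against 0.745 simulated.

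**The case against.** The strongest reply is that the comparison is not blind. Heaping, large random error and a common default entry all reshape the distribution, as the last three rows of the table show. The Background section lists digit preference among the causes of poor recall, and a shape comparison can register it. Wholesale swapping of dates between women is also unlikely, since each participant has her own calendar or phone. And comparing distributions could be read to include the means, which would reveal a constant shift.

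Much of this stands. A reader might infer that the method cannot detect any disagreement, or that every useless tool would pass. That is too strong. What remains is that shuffled or unrelated dates would escape even with means added, that the named statistics miss a constant shift, and that a detected shape difference is not a measure of inaccuracy.

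A reader might also infer that the trial's main conclusion, or a decision to scale up, rests on this comparison. The documents do not support that. The primary outcome compares each woman's recall with her own actual date and does not use these statistics. The Abstract links evidence for scale-up to the success of the interventions, and the objectives frame that as better recall. No section makes the skewness and kurtosis result a criterion.

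Finally, it may be said that handling of cycles without a tool entry belongs in an analysis plan. That is fair. It is raised here only as part of the remedy, not as an omission.

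**Conclusion.** The point holds for the additional tool-validation analysis. The statistics named in the article describe marginal shape and do not measure agreement within a woman. A constant shift, dates shuffled between women, or unrelated dates of the same spread would go unnoticed, with as few as 0% to 10% of dates within ±1 day in the simulated cases. Errors that change the shape can show, but without a usable size.

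Invariance to shift and re-pairing is algebraic and rests on no assumption. The percentages rest on an assumed uniform 30-day window. The effect of random error depends heavily on the window: for SD 5 days the change in kurtosis runs from about 0.08 (90 days) to about 0.53 (30 days).

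This should be fixed before the tools are reported as validated. It does not threaten the primary or secondary outcome.

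**What to change.** Replace the skewness and kurtosis sentence with a paired analysis. For the endline surveillance period, match tool and surveillance start dates by participant and cycle, under a matching rule set in advance. Report for each tool:
- the proportion of matched cycles within ±1 day, with a confidence interval that allows for clusters and for repeated cycles within a woman;
- the mean difference (tool minus surveillance) with limits of agreement;
- the share of surveillance cycles with no tool entry.

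Skewness and kurtosis may stay as a descriptive check for heaping, but not as the validation criterion.

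The cost is a change of analysis wording and some linkage work. No new data collection is needed. All three tools record start dates, the article says tool data are extracted regularly, and it places the endline surveillance before implementation ends, so the two sources should overlap. The baseline surveillance preceded the interventions and cannot be used. When the article's project update was written, endline data collection was still to start (mid-September 2018), so the pairs were not yet in hand and the change could be made before any analysis.

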#### Data safety monitoring plan (DSMP)

We anticipate no risk of interventions. Validity and integrity of the data is being ensured by appropriate research design, use of pretested and validated tools for data collection and by quality assurance.

#### Data confidentiality and archiving

Privacy, anonymity and confidentiality of data is strictly being maintained. In order to protect the safety of participants, all trial related information is being kept confidential and stored securely at the central office in icddr,b. Coded identification is used to anonymise and depersonalise the data. The linking code, electronic data files and paper forms are stored in a separate location under password protections or lock and key. Access to the data will be limited to the small number of individuals including the investigators, statisticians, quality control team and audit.

#### Dissemination policy

The trial results will be communicated and published irrespective of the outcome of the trial upon approval from all the investigators, implementing organizations and funding bodies.

### Project update

Enrolment of study participants continued from January 24, 2017 till March 29, 2017. Baseline data collection commenced from April 2017 and was completed in October, 2017. Implementation of interventions started from October 2017 and are currently ongoing. Endline data collection will start from mid-September, 2018.

## Discussion

This trial is expected to generate evidence on efficacy of calendar, SMS and smart phone application system for improving accuracy of LMP-recall in rural settings. Although calendar, or menstrual dairies has already been tried in clinical settings for recording menstrual dates, public health implication of using these tools for recording LMP is yet to be explored [16, 23]. The nationwide coverage of mobile phone networks, relatively cheaper tariff and increasing use of smart phone among general population including the poor, presets m-health as a potential solution to address this issue. [3, 23–25].

## Abbreviations

ANC: Antenatal care
BMGF: Bill Melinda Gates foundation
DSS: Demographic surveillance system
GA: Gestational age
icddr,b: International centre for diarrhoeal disease research, Bangladesh
LMIC: Low and middle income countries
LMP: Last menstrual period
USG: Ultrasonography
